# Follow-up after surgical treatment for intermittent claudication (FASTIC): a study protocol for a multicentre randomised controlled clinical trial

**DOI:** 10.1186/s12912-020-00437-7

**Published:** 2020-06-04

**Keywords:** Intermittent claudication, Secondary prevention, Medication adherence, Vascular nursing, Person-centred care, Randomised controlled trial, atherosclerosis

## Abstract

**Background:**

Intermittent claudication (IC) is a classic symptom of peripheral arterial disease, and strongly associated with coronary heart disease and cerebrovascular disease. Treatment of IC and secondary prevention of vascular events include best medical treatment (BMT), changes in lifestyle, most importantly smoking cessation and increased physical exercise, and in appropriate cases surgery. A person-centred and health promotion approach might facilitate breaking barriers to lifestyle changes and increasing adherence to secondary prevention therapy. The FASTIC study aims to evaluate a nurse-led, person-centred, health-promoting follow-up programme compared with standard follow-up by a vascular surgeon after surgical treatment for IC.

**Methods:**

The FASTIC-study is a multicentre randomised controlled clinical trial. Patients will be recruited from two hospitals in Stockholm, Sweden after surgical treatment of IC through open and/or endovascular revascularisation and will be randomly assigned into two groups. The intervention group is offered a nurse-led, person-centred, health-promoting programme, which includes two telephone calls and three visits to a vascular nurse the first year after surgical treatment. The control group is offered standard care, which consists of a visit to a vascular surgeon 4–8 weeks after surgery and a visit to the outpatient clinic 1 year after surgical treatment. The primary outcome is adherence to BMT 1 year after surgical treatment and will be measured using The Swedish Prescribed Drug Registry. Clinical assessments, biomarkers, and questionnaires will be used to evaluate several secondary outcomes, such as predicted 10-year risk of cardiovascular and cerebrovascular events, health-related quality of life, and patients’ perceptions of care quality.

**Discussion:**

The FASTIC study will provide important information about interventions aimed at improving adherence to medication, which is an unexplored field among patients with IC. The study will also contribute to knowledge on how to implement person-centred care in a clinical context.

**Trial registration:**

ClinicalTrials.govNCT03283358, registration date 06/13/2016.

## Introduction

Intermittent claudication (IC) is a classic symptom of peripheral arterial disease (PAD), which is caused by atherosclerosis, and leads to decreased arterial circulation to the lower extremities. Clinical symptoms of PAD vary from atypical claudication with inconsistent leg discomfort on effort, IC with pain induced by exercise, to critical limb ischaemia (CLI) with ischaemic rest pain and ulceration or gangrene. Age, heredity, lifestyle (smoking, diet, and lack of exercise), high blood pressure, and diabetes are some of the risk factors that contribute to formation of atherosclerosis [1, 2]. IC is strongly associated with coronary heart disease and cerebrovascular disease. Symptoms of atherosclerotic disease from the lower extremities can be an early predictor of all-cause and cardiovascular-related mortality [3].

IC affects approximately 7% of all adult individuals older than 60 years [4]. PAD results in chronic pain, impaired walking ability, restricted mobility, and reduced ability to perform daily activities. People suffering from IC are burdened by social isolation, fatigue, and a sense of dependency, resulting in decreased quality of life [5, 6].

Treatment of IC aims at symptom relief, increased walking ability, increased health-related quality of life (HRQoL), and secondary prevention of vascular events. Management of IC according to clinical guidelines, include best medical treatment (BMT), changes in lifestyle, most importantly smoking cessation and increased physical exercise, and in appropriate cases, revascularisation through surgical or endovascular methods [1, 2, 7]. An increased treadmill walking capacity can be achieved when endovascular therapy is added to medical therapy or supervised exercise during early and intermediate follow-up [8]. Fahkry et al. showed that combination therapy with endovascular revascularisation in addition to supervised exercise provides superior improvement in walking distance and HRQoL compared with supervised exercise alone [9].

Regardless of the need for revascularisation, those diagnosed with IC should be treated with BMT to prevent progression of disease and reduce the risk for cardiovascular and cerebrovascular complications and death [7]. BMT for patients with IC includes antiplatelet agents, lipid-lowering agents, and antihypertensive treatment in the presence of hypertension [1, 10]. A large meta-analysis showed a 23% reduction in risk, using antiplatelet agents, of serious cardiovascular events in 9214 patients with PAD [11]. An observational, retrospective cohort study that analysed data from the Swedish national health care registries showed that only 65% of the patients with IC were offered BMT, which was defined as any antiplatelet or anticoagulant therapy along with statin treatment [12].

### Scientific background

Complex interventions are widely used in the health service and defined as interventions.

which comprise multiple interacting component [13]. Medical Research Council (MRC) guidelines for developing and evaluating complex interventions provide guidance to researchers and strengthen the internal and external validity and add value to health care research. Several steps are recommended for the systematic development of complex interventions such as problem identification, the systematic identification of evidence, identification or development of theory, determination of needs, the examination of current practice and context, modelling the process and expected outcomes leading to final element: the intervention design [13, 14].

Person-centred care (PCC) is a method of care-giving that has been implemented over the last few years. It has been shown to improve self-efficacy, adherence to prescribed medication and shorten hospital stay [15]. Person-centred care (PCC) means involvement of the patients as partners in their care. The core of a person-centred approach is allowing the patient to be part of their care by letting them describe their situation from their own point of view and putting their views at the centre of care. This could also be described as a collaborative process of decision-making between patients and their health care provider that takes into account the patient’s values and preferences and clinical evidence [16]. A personal health plan is made based on the information exchanged during the narrative communication. This health plan includes goals, strategies, and terms of evaluation, and is jointly developed by the patient and the professional [17]. The process of practicing PCC in health care as described by Ekman et al. contains three components: patient narratives, partnership, and safeguarding the partnership [17]. Patient narratives is about sharing of information and initiating partnership between the patient and the care giver. Narrative communication involves learning from each other, creating common understanding of the illness, and learning about the patient’s resources, limitations, and expectations. This provides the professional a good basis for discussing and planning care and treatment with the patient [17]. A person-centred care approach added to the usual care of patients with acute coronary syndrome improves general self-efficacy, which is an important factor for effective self-management of illness [18].

Effective public health, health promotion, and chronic disease management programmes help people maintain and improve health, reduce disease risks, and manage chronic illness. Health behaviour theory can play a critical role throughout the programme planning process and for the effect of the intervention. According to social cognition theory, self-efficacy, goals, and outcome expectancies are three main factors that can affect the possibility that a person will change a health behaviour are [19].

Secondary prevention therapy requires engagement, participation, and adherence from the patient. Patients with PAD require disease-specific information, adequate support enabling them to manage recommended behavioural changes [20] and to adapt to and live with chronic illness [21]. A large international registry on patients with established atherosclerosis reported an association between non-adherence to evidence-based secondary prevention therapies and a significant increase in risk for long-term adverse events, including mortality [22]. Adherence to medication has been reported to be as low as 30% [23] to 50% [22]. Non-adherence to medication after acute coronary syndrome tends to be lower immediately after discharge (20%) and increases to 54 and 53% at 6 months and 1 year after discharge, respectively [24]. Barriers to physical activity in patients with PAD are related to the pain experienced when walking [25], lack of knowledge about the condition and doubts that lifestyle changes, particularly physical activity, would improve their condition [20]. Therefore, providing clear and consistent information about the condition and detailed information regarding exercise, as well as mental support to enable behavioural changes, are important [20]. Furthermore, preventive treatment measures require a long-term follow up. A 20-min visit with a vascular surgeon in the standard follow-up after surgical intervention offers limited time to address the important questions of physical exercise, smoking, and medical adherence. Probably not all the patient’s barriers to lifestyle changes and medical adherence are identified in such a visit. A person-centred and health promotion approach might facilitate breaking barriers and increasing adherence to secondary prevention therapy for patients with IC. However, to the best of our knowledge, no such studies have been performed.

### Hypothesis

We hypothesise that a nurse-led, person-centred, health-promoting follow-up programme will increase adherence to BMT and reduce the risk for cardiovascular or cerebrovascular events compared with standard care.

## Methods/design

### Objectives

The overall aim of the FASTIC study is to evaluate a nurse-led, person-centred, health-promoting follow-up programme compared with standard follow-up by a vascular surgeon after surgical treatment for IC.

The primary objective of the FASTIC study is to examine the effect of the above-mentioned programme on the patient’s adherence to prescribed BMT (primary outcome) and reduce the risk for cardiovascular or cerebrovascular events. Furthermore, secondary objectives of the FASTIC study are to investigate the effect of the above-mentioned programme on patient-reported outcomes (HRQoL, health literacy, belief of medication, and adherence to medication), health outcomes, and participants’ experience of the intervention programme compared with the standard follow-up.

### Study design and setting

The FASTIC study is a multicentre, randomised controlled clinical trial. Patients will be recruited from two sites; the Departments of Vascular Surgery at Södersjukhuset and at Karolinska University Hospital, both in Stockholm, Sweden. Patients with IC are referred to the vascular surgical outpatient clinics in one of these hospitals by a primary care physician.

The Stockholm County is a geographical area covering the City of Stockholm and surrounding area with approximately 2.3 million inhabitants. This region has two centres for vascular surgery, the Karolinska University Hospital and Södersjukhuset, both of which are located near the city centre. On average, 350 open surgical interventions and endovascular interventions for patients with IC are performed at these two centres every year according to the Swedish National Registry for Vascular Surgery (Swedvasc). No major vascular surgery is performed outside these centres and all patients in the Stockholm County with IC who may require arterial surgical intervention are referred to one of these centres. During the first visit at the vascular surgical outpatient clinic, diagnosis and requirement for revascularisation are decided by a vascular surgeon and recorded in the patient’s medical record. This decision is based on clinical symptoms and circulatory assessments, including the ankle brachial index (ABI), Duplex ultrasound, and/or computed tomography angiography. Cessation of smoking for at least 3 months prior to surgery is required. Patients are prescribed statins and antiplatelet agents at this point if not previously prescribed.

### Eligibility criteria

Patients who fulfil all the inclusion criteria and none of the exclusion criteria mentioned below are eligible for the study.

#### Inclusion criteria

Age of 18 years and olderDiagnosed with IC (ICD-10 Diagnosis Code I70.2 or I739B) by a vascular surgeonNo symptoms or signs of critical limb ischaemia (rest pain, ulceration, or gangrene)Scheduled for revascularisation through open and/or endovascular surgeryAbility to speak and understand Swedish language

#### Exclusion criteria

Diagnosed with dementiaPlanned discharge to a nursery homeNot accountable for administrating their own medicationsA survival expectancy less than 1 year

### Sample size

The sample size was calculated based on results from previous literature regarding primary outcome (adherence to medication) in cardiological studies [22, 26]. Statistical power analysis using IBM SPSS Sample Power 3 (IBM Corp., Armonk, NY, USA) showed that a required sample size of 186 participants was needed to detect a statistically significant increase in adherence to prescribed BMT from 50 to 70% (power, 0.80; significance value, 0.05; two-sided). We plan to recruit 210 participants and expect a 10% drop-out.

### Recruitment

Patients who are eligible for the study are identified by one of the study nurses at each of the two outpatient clinics. Written information about the FASTIC study, including a consent form, is sent by mail to the eligible patients. When the patients arrive to the vascular surgical ward prior to surgery, the study nurse provides oral information about the study and asks for participation. If consent is obtained, baseline data are collected. The surgery is performed and randomisation to either an intervention programme (intervention group) or a standard care programme (control group) is performed immediately after surgery by a study nurse. In some cases, the endovascular procedure may not result in revascularisation. The patient can still be randomised to the FASTIC study if a decision is made to reschedule to open surgery. If no further surgical interventions are planned, the patient will be withdrawn from the study. Figure 1 shows a description of the study flow. A time schedule of study enrolment, interventions, and assessments is shown in Fig. 2.

**Fig. 1 Fig1:**
[figure not shown]
Study flow diagram of enrolment and randomisation

**Fig. 2 Fig2:**
[figure not shown]
SPIRIT schedule of enrolment, interventions, and assessments

### Randomisation

Randomisation is performed by sequence generation using secure computer-generated random numbers. The allocating study nurses have no insight to block randomisation factors behind the sequence generation process. Patients who meet all study criteria and consent to participate are randomised to either the intervention group or the control group. No blinding will be applied in this study.

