### Statistical analysis

Descriptive statistics will be used to describe baseline demographic and clinical data. Continuous variables will be summarised as mean (SD) or median (interquartile range), and categorical variables will be summarised as number (percentage). Comparisons between the intervention group and the control group will be made using the t-test and ANOVA for repeated measures, or the Wilcoxon rank-signed test and Kruskall–Wallis test according to the underlying distribution for continuous data. The chi-square or Fischer’s exact test will be used for categorical data. Logistic regression analysis will be performed for binary outcomes to adjust for confounding factors. All analyses will be performed according to the intention-to-treat principle. IBM SPSS version 23 or later (IBM Corp., Armonk, NY, USA) will be used for statistical analyses. The CONSORT 2010 statement will be followed when reporting the results [46].

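### Two hospitals and blocked allocation, but no between-arm test is stated to include hospital or a blocking factor; if hospital is prognostic, the pooled comparison forgoes some power

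*Protocol article*

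**What the plan says.** - **Allocation** (Randomisation): "The allocating study nurses have no insight to block randomisation factors behind the sequence generation process". Patients are "randomised to either the intervention group or the control group". The factors are not named, no allocation ratio is given, and nothing says that blocks were formed within hospital.
- **Centres** (Study design and setting): "Patients will be recruited from two sites".
- **Tests** (Statistical analysis): t-test, repeated-measures ANOVA or rank tests for continuous data, and chi-square or Fisher's exact test for categorical data. None is described with a hospital or blocking term. One adjusted model is named: "Logistic regression analysis will be performed for binary outcomes to adjust for confounding factors". Its covariates are not listed. No adjusted model is named for continuous outcomes.
- **Size** (Sample size): "a required sample size of 186 participants was needed". The target effect is a rise in adherence of 20 points, from 50% to 70%, with 80% power at a two-sided level of 0.05. On recruitment the section adds: "We plan to recruit 210 participants and expect a 10% drop-out".

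**The concern.** The usual principle is that the analysis should reflect the way patients were allocated. Here the tests named for comparing the arms are pooled over hospitals. The stated reason for adjusting is confounding, and a factor balanced by design is not a confounder, so a reader who follows the section literally has no prompt to include hospital or a blocking factor.

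If adherence differs between the two hospitals, a pooled test leaves that variation in its error term, and a test stratified by hospital removes it. At stake is power for the primary outcome. There is little to spare: 210 × 0.90 = 189 expected completers against 186 required. Recruitment is reported as complete, so the analysis is the main place left to protect power.

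**Working it through.** **Inputs from the article.** Adherence 0.50 against 0.70, power 0.80, two-sided 0.05, total 186, two hospitals.

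**Assumptions.** 1:1 allocation (it reproduces 186), hospitals of equal size, and a hospital difference in adherence *g* of 0 to 40 percentage points. The article gives none of these.

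**1. The plan's own figure.** With pooled variance and no continuity correction:

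n per arm = [1.960 × √(2 × 0.6 × 0.4) + 0.842 × √(0.5 × 0.5 + 0.7 × 0.3)]² / 0.20² = (1.358 + 0.571)² / 0.04 ≈ 93

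This gives 186 in total. The stated figure reproduces, and it rests on an unstratified comparison of two proportions.

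**2. Power, pooled chi-square against Cochran-Mantel-Haenszel (CMH) by hospital, 93 per arm, by simulation.**

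| Setting | g | Pooled | CMH | Gain (points) |
|---|---|---|---|---|
| A. Blocks within hospital, odds ratio 7/3 in each | 20 | 0.775 | 0.790 | 1.5 |
| | 30 | 0.738 | 0.773 | 3.5 |
| | 40 | 0.675 | 0.737 | 6.2 |
| B. Blocks within hospital, 20-point effect in each | 0 | 0.800 | 0.796 | −0.4 |
| | 10 | 0.802 | 0.803 | 0.1 |
| | 20 | 0.803 | 0.818 | 1.4 |
| | 30 | 0.808 | 0.838 | 3.1 |
| | 40 | 0.821 | 0.871 | 5.0 |
| C. Blocks ignore hospital, 20-point effect in each | 0 | 0.801 | 0.799 | −0.2 |
| | 10 | 0.800 | 0.803 | 0.3 |
| | 20 | 0.800 | 0.817 | 1.7 |
| | 30 | 0.796 | 0.836 | 3.9 |
| | 40 | 0.799 | 0.870 | 7.1 |

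Gains were taken before rounding. The stratified test gains in all three settings once *g* reaches 20 points. Power is lower in A because a fixed odds ratio shrinks the overall difference. At g = 20, control adherence is 0.60 and 0.40. Multiplying the odds by 7/3 gives 0.778 and 0.609, mean 0.693, a difference of 19.3 points instead of 20. Stratifying does not recover that part.

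**3. Type I error of the pooled test if blocks were formed within hospital.** With equal hospitals, the within-hospital variance is p(1 − p) − g²/4. The pooled standard error is then too wide by the factor √{p(1 − p) / [p(1 − p) − g²/4]}. At p = 0.6:

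- g = 20: √(0.24 / 0.23) = 1.022, or 2.2% too wide
- g = 30: √(0.24 / 0.2175) = 1.051, or 5.1%
- g = 40: √(0.24 / 0.20) = 1.095, or 9.5%

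The true two-sided level is 2 × [1 − Φ(1.960 × factor)] = 0.045, 0.040 and 0.032. Simulation gives 0.046, 0.039 and 0.031 at a common adherence of 60%, and about 0.043, 0.038 and 0.031 at 50%. CMH stays at about 0.05.

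**4. Type I error if blocks were not formed within hospital.** The pooled test gives 0.048 to 0.049 in simulation at 60% adherence, and 0.047 to 0.048 at 50%, across the whole range of *g*. It is valid.

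**5. Logistic regression.** With a hospital log odds ratio of 1, adding hospital raises the treatment log odds ratio from 0.847 to 0.898 and its standard error from 0.307 to 0.317. The ratio z moves from 2.76 to 2.83. Power rises slightly, but the interval for the log odds ratio does not narrow.

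**The case against.** **The blocking factors may be no more than block sizes.** The sentence concerns concealment from the nurses, and no section says that allocation was stratified by hospital. This stands. A reader might infer that balance by hospital was built in and that the reported intervals and p-values are therefore too wide. The article does not support that: step 4 shows a valid pooled test if blocks ignored hospital. Plain blocks without strata matter only if the outcome drifts over time.

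**The logistic model may include hospital.** This also stands. It would be too strong to say that every planned comparison ignores hospital. The primary outcome was sized as a proportion, so the logistic model can apply to it, and its covariates are open.

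**The covariate list can be left to an analysis plan.** A full list can, and its absence is not the point. The article does commit to specific pooled tests, and it gives a reason for adjustment that does not cover design factors.

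**The planned power is not lost.** A reader might take setting A to mean that pooling erodes the stated 0.80. Under the planned 20-point difference, pooled power stays at about 0.80 or above (settings B and C). What is forgone is a gain.

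**A large hospital difference is unlikely.** Both centres serve one county, both arms receive guideline-directed care, and adherence comes from one national registry. Differences of 30 to 40 points are pure assumption. This limits the size of the point. It does not count against stratifying, which costs almost nothing.

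**Conclusion.** The point holds as a matter of efficiency. None of the between-arm tests is stated to include hospital or a blocking factor, and the one adjusted model is reserved for confounders. If hospital is prognostic, the pooled primary comparison forgoes about 1.5 points of power at a 20-point hospital difference and 3 to 6 points at 30 to 40 points when blocks were formed within hospital. If they were not, the gain forgone at 30 to 40 points is 4 to 7 points. At 10 points or less nothing material is lost.

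Conservative testing on the difference scale is a conditional addition. It applies only if blocks were formed within hospital, which is not stated, and it does not carry over to the logistic odds ratio. In no setting examined is the type I error inflated.

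These sizes rest on assumed hospital differences, equal hospital sizes and 1:1 allocation. With a 70/30 hospital split the excess width in step 3 is somewhat smaller: 1.8%, 4.2% and 7.8%.

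**What to change.** In Statistical analysis, or in the analysis plan before outcome data are examined:

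1. State what the blocking factors were and whether blocks were formed within hospital.
2. Make the primary adherence comparison stratified by hospital and by any factor used to stratify the randomisation, with a Cochran-Mantel-Haenszel test or a logistic model that contains these terms.
3. Put the same terms in the models for continuous outcomes.
4. Keep the pooled chi-square test as supportive.

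The cost is a few lines of text, one degree of freedom per factor, and a power loss of at most about 0.4 points if hospital turns out not to be prognostic (0.800 against 0.796 in setting B). The recruiting hospital is known for every participant, so no new data are needed, and the sample size stays at 186. Fixing the terms in advance also removes discretion over what enters the adjusted model in an unblinded trial.

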#### Adherence to medication

The primary outcome, adherence to medication, is defined as adherence to prescribed antithrombotic agents and lipid modifying agents 1 year after revascularisation.

The Swedish Prescribed Drug Registry (PDR) will be used for collecting data on medication adherence. The PDR provides data on prescribed drugs containing information on dispensed items, dispensed amount, dosage, and expenditure. Furthermore, this registry has been linked to the civic registry number since 2005 and thus provides information on an individual basis. This registry does not include medications that are prescribed and administered in hospitals [31]. Data from a period of 18 months (6 months before to 12 months after revascularisation) will be retrieved from the PDR for each participant. The WHO Collaborating Centre for Drug Statistics Methodology classification of Anatomical Therapeutic Chemical (ATC) codes will be used to identify antithrombotic agents and lipid-modifying agents (see Table 1 for specific codes). Although antihypertensive medications will not be included in the analysis for primary outcome, they can be considered as BMT for patients with hypertension. Information on antihypertensives will be retrieved from the PDR as medication of interest for the study. We will also collect patient-reported adherence to medication (anticoagulant agents, antiplatelet agents and lipid-lowering agents) at study enrolment and at 1 year after revascularisation.

**Table 1 Tab1:** Medications of interest in the study

Medication group	ATC Code
Antithrombotic agents	
Vitamin K antagonists	B01AA
Heparin group	B01AB
Platelet aggregation inhibitors excluding heparin	B01AC
Direct thrombin inhibitors	B01AE
Direct factor Xa inhibitors	B01AF
Lipid-modifying agents	
HMG CoA reductase inhibitors	C10AA
Fibrates	C10AB
Other lipid-modifying agents	C10AX
Antihypertensives	
Diuretics	C03
Beta-blocking agents	C07
Calcium channel blockers	C08
ACE inhibitors, plain	C09A
ACE inhibitors, combinations	C09B
Angiotensin II antagonists, plain	C09C
Angiotensin II antagonists, combinations	C09D

legend: Medications of interest in the study and their Anatomical Therapeutic Chemical (ATC) codes according to the WHO Collaborating Centre for Drug Statistics Methodology (WHOCC) classification*.*

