### Trial status

The FASTIC trial is currently ongoing with data collection in both study sites. Recruitment of participants started in June 2016 and was completed in November 2018.

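### The unqualified no-blinding statement also covers derivation and analysis of the registry-based primary outcome, where masking to allocation is possible and cheap

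*Protocol article*

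**What the plan says.** The Randomisation section ends with "No blinding will be applied in this study". It does not separate patients and nurses from whoever derives or analyses the outcome. Allocation concealment is a different matter, and the same section deals with it: "The allocating study nurses have no insight to block randomisation factors behind the sequence generation process".

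Under Adherence to medication, the primary outcome "is defined as adherence to prescribed antithrombotic agents and lipid modifying agents 1 year after revascularisation". Its source is a register: "The Swedish Prescribed Drug Registry (PDR) will be used for collecting data on medication adherence". On content, "The PDR provides data on prescribed drugs containing information on dispensed items, dispensed amount, dosage, and expenditure", and on the period, "Data from a period of 18 months (6 months before to 12 months after revascularisation) will be retrieved from the PDR for each participant". The section also fixes the ATC codes and notes that drugs given in hospital are not captured. The Sample size section treats the outcome as a proportion, 50% against 70%.

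The Data management section says that participants can be identified in the study data only by study number. The Statistical analysis section neither provides for nor excludes a masked analyst. On timing, the Trial status section says "Recruitment of participants started in June 2016 and was completed in November 2018".

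**The concern.** An open trial gains credibility where its primary outcome is handled without knowledge of the arm. Here that is feasible. A nurse-led follow-up programme cannot be concealed from patients or staff, but a file of dispensing records can be processed without an allocation column.

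Turning dispensing dates, amounts and dosages into adherent or not adherent takes decisions. The article itself raises one source of them, the periods in hospital that the register does not cover. Others are my own expectation of such data: days' supply, switches within a class, and how the two drug groups are combined. If such decisions are taken with arms visible, a critic can discount a positive primary result on that ground alone.

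This concerns a stated policy, not a missing detail. If an analysis plan does provide for masked derivation, it conflicts with the sentence in the article, and the sentence still needs correcting.

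**Working it through.** **1. The plan's own figure.** Inputs from Sample size: 50% against 70%, power 0.80, two-sided 0.05. Equal allocation is my assumption. With pooled variance and no continuity correction,

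n per arm = [1.96·√(2·0.6·0.4) + 0.842·√(0.5·0.5 + 0.7·0.3)]² / 0.20² = (1.358 + 0.571)² / 0.04 ≈ 93.

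The total is 186, as stated. Of the planned 210, a 10% loss leaves 189, about 94 per arm. Masking changes none of these figures.

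**2. Who has to be unblinded.**

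| Role | Must know the arm? | Covered by the sentence as written? |
|---|---|---|
| Patient, nurse, surgeon | Yes, by the nature of the programme | Yes |
| Person deriving adherence from register records | No | Yes, no exception made |
| Analyst, up to dataset lock | No | Yes, no exception made |

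The register is individually linked ("this registry has been linked to the civic registry number since 2005 and thus provides information on an individual basis") and study data are keyed by study number. Withholding the allocation column therefore looks practicable, although the documents do not discuss it.

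**3. Sensitivity of the result to coding (hypothetical).** With 94 per arm and 60% pooled adherence, the smallest significant difference is about

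1.96·√(0.6·0.4·2/94) = 1.96·0.0715 = 0.140, or 14 points.

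Moving k patients up in one arm and k down in the other shifts the difference by 2k/94. The starting point below, 52/94 against 61/94, and the values of k are assumptions:

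| k per arm | Counts | Difference | Shift from start | z | p |
|---|---|---|---|---|---|
| 0 | 52 v 61 | 9.6 points | 0 | 1.34 | 0.18 |
| 1 | 51 v 62 | 11.7 points | 2.1 | 1.64 | 0.10 |
| 2 | 50 v 63 | 13.8 points | 4.3 | 1.94 | 0.053 |
| 3 | 49 v 64 | 16.0 points | 6.4 | 2.23 | 0.025 |

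The standard error is the same in each row, because the pooled proportion stays at 113/188: √(0.601·0.399·2/94) = 0.0714.

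**4. Choosing among definitions (hypothetical).** A rule applied to both arms does not reclassify patients in opposite directions by arm, so step 3 does not describe the choice of a definition. A simulation under no true effect comes closer to it. It used 93 per arm, 50% adherent under every definition, K candidate definitions with latent correlation 0.5 to 0.95, and 20,000 trials per setting. A single definition rejected in about 4.7% of trials.

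| K | Any two-sided p < 0.05 | Any significant result favouring the intervention (nominal 2.5%) |
|---|---|---|
| 2 | 7–9% | about 4% |
| 3 | 9–13% | 5–6% |
| 5 | 12–19% | 6–9% |

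These rates apply only if the best-looking definition is picked after seeing results by arm. Nothing in the documents says that this happens.

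**5. Timing.** Recruitment ended in November 2018, so the last 12-month windows close around November 2019. The article appeared in June 2020. A rule not fixed by then could have been set after outcome data existed. The article does not date the register extraction or the rule, and Trial status describes data collection as ongoing.

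**The case against.** The strongest reply is that the sentence closes a paragraph on patient allocation and can be read as an ordinary open-label statement. The coding rule and the order of data lock normally belong in an analysis plan, which is not shown, so their absence from an article is no fault. If the rule was fixed in advance and is applied by code, visible allocation leaves little discretion. The outcome also has real protection already: an external register records dispensing, and the drug codes, window and time point are fixed.

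Most of this stands, and it limits the point. A reader might infer that adherence will in fact be coded with arms visible. The documents do not support that, since they name neither who derives the variable nor when. A reader might also infer that the dispensing rule is still open, and that cannot be known without the analysis plan. Nor is the primary outcome the only objective one: the Biomarkers section lists blood tests and exhaled carbon monoxide.

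What the reply does not remove is the sentence itself. It is absolute, and it covers roles for which openness serves no purpose.

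**Conclusion.** The point holds in a limited form. The article excludes all blinding when only patients and care providers need be unblinded, and so permits open coding and analysis of the primary outcome. The exposure is to coding and definition choices, not to how dispensing is captured, and it shrinks to little if an unseen plan fixes the algorithm before data access. Allocation concealment and sample size are unaffected.

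The size cannot be derived from the documents. The 14-point threshold assumes 94 per arm and 60% pooled adherence. The 6-point shift and the simulated error rates rest on scenarios of my own. They show how few borderline patients could matter and should not be read as an expected bias. The change is worth making because it is cheap, not because bias has been shown.

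**What to change.** Replace the sentence with:

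*Patients and care providers are not blinded. The PDR adherence variables are derived under a pre-specified rule and the primary dataset is locked with allocation removed; arm codes are merged only after lock.*

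If derivation has already taken place, state whether it was masked. If an analysis plan already fixes the rule, cite it with its date.

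The cost is one added step in data handling: holding back the allocation column until lock. It needs no extra staff and changes neither the sample size nor patient care.
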